## Abstract

**Background:**

Providing ongoing family centred support is an integral part of childhood cancer care. For families living in regional and remote areas, opportunities to receive specialist support are limited by the availability of health care professionals and accessibility, which is often reduced due to distance, time, cost and transport. The primary aim of this work is to investigate the cost-effectiveness of videotelephony to support regional and remote families returning home for the first time with a child newly diagnosed with cancer

**Methods/design:**

We will recruit 162 paediatric oncology patients and their families to a single centre randomised controlled trial. Patients from regional and remote areas, classified by Accessibility/Remoteness Index of Australia (ARIA+) greater than 0.2, will be randomised to a videotelephone support intervention or a usual support control group. Metropolitan families (ARIA+ ≤ 0.2) will be recruited as an additional usual support control group. Families allocated to the videotelephone support intervention will have access to usual support plus education, communication, counselling and monitoring with specialist multidisciplinary team members via a videotelephone service for a 12-week period following first discharge home. Families in the usual support control group will receive standard care i.e., specialist multidisciplinary team members provide support either face-to-face during inpatient stays, outpatient clinic visits or home visits, or via telephone for families who live far away from the hospital. The primary outcome measure is parental health related quality of life as measured using the Medical Outcome Survey (MOS) Short Form SF-12 measured at baseline, 4 weeks, 8 weeks and 12 weeks. The secondary outcome measures are: parental informational and emotional support; parental perceived stress, parent reported patient quality of life and parent reported sibling quality of life, parental satisfaction with care, cost of providing improved support, health care utilisation and financial burden for families.

**Discussion:**

This investigation will establish the feasibility, acceptability and cost-effectiveness of using videotelephony to improve the clinical and psychosocial support provided to regional and remote paediatric oncology patients and their families.

## Background

The Royal Children's Hospital (RCH) Haematology, Oncology and Stem Cell Transplant Unit is the major tertiary paediatric referral centre for Queensland, northern New South Wales and the southwest Pacific. A multidisciplinary team of medical, nursing and allied health professionals provides care and support to children with cancer, as well as their families. Each year the service cares for around 100 newly diagnosed patients.

Childhood cancer presents a major life stressor for the entire family [1,2]. Significant changes to the everyday lives of families, practically, socially and emotionally, cause major disruption [3-5]. There is evidence that this disruption results in isolation and poor communication between family members, anxiety, low self-esteem and school problems for siblings [6] and anxiety, post-traumatic stress symptoms and risk of depression for parents [7,8]. Families supporting home care of their child are faced with personal and financial sacrifice, higher risk of fatigue and burnout, and the prospect of managing significant symptomatology in their child. Their own mental and emotional health is directly affected [9] as they experience high levels of depression and anxiety. Providing ongoing support to these families is an essential part of care [10-13].

Around 60% of the families cared for by the RCH (Figure 1) live in regional and remote areas (based on post code and corresponding ARIA+ score – Accessibility/Remoteness Index of Australia [14,15]. For families living in regional and remote areas, the opportunities to receive specialist support are inhibited by a number of factors [16] These include: availability of health care professionals [17] and accessibility due to distance, time, cost and transport [18]. One possible solution is the use of online support mechanisms, such as videotelephony, to help give much needed support to patients, parents, siblings and the family as a whole.

**Figure 1 F1:**
[figure not shown]
Proportion of newly diagnosed paediatric oncology patients in major cities and regional and remote areas (data provided by the Royal Children's Hospital January 2004 to January 2006, n = 180).

Studies investigating the use of videotelephony to date have been mostly small scale projects focusing on feasibility. The potential of videotelephony in adult home nursing has been shown in pilot trials in the UK [19], the US [20] and in Australia [21]. Low-quality compressed video can be used to support care directly to the home. One small study (n = 20) identified that whilst there are activities that cannot be conducted by videotelephone, those that can coincide with the typical interactions occurring in face-to-face home visits [22].

A larger scale exploratory investigation into the use of videotelephones for psychotherapy (n = 80) reported higher scores for client levels of initiative, trust and spontaneity via videotelephone than the same scores obtained for face-to-face therapy [23]. Although this study did not deliver services directly to patient homes (instead patients were assessed via videotelephone between separate rooms in the treating facility) it does provide evidence that videotelephony can be used to provide the type of personal psychosocial support required by paediatric oncology patients and families. The most extensive study using videotelephones to support adult home care (n = 212) [24] showed that:

• clinical and educational services can be delivered successfully using videotelephones and the standard home telephone network

• the quality of care delivered via virtual videotelephone home visits was comparable to face-to-face home visits with the added benefit of cost savings.

The only other evidence in the literature is in the area of adult oncology. Videotelephones have been used successfully since 1998 to provide direct patient care and supportive care [25], as well as supporting palliative care delivery for patients in their home [26,27]. This has been shown to be a cost-effective service delivery method [28]. A large randomised controlled trial in adult palliative care is also underway in Canada [29]. To date there have been no published studies investigating the use of videotelephony for supporting paediatric oncology families.

### Hypotheses

1. Videotelephony will be a feasible and acceptable mode of service delivery to regional and remote paediatric oncology families

2. Support provided using videotelephony to regional and remote paediatric oncology families will be as effective as support provided via traditional mechanisms to metropolitan families

3. Using videotelephony will be a cost-effective method of service delivery.

## Methods/design

### Design

This study is a randomised controlled trial using three-groups: (1) Regional and remote intervention group, (2) Regional and remote control group, and (3) Metropolitan control group. Families will be classified as either metropolitan or regional and remote based on the ARIA+ score using the post code of the family's primary place of residence. Regional and remote families will be randomly allocated either to the intervention (1), or to a usual support control group (2). Metropolitan patients will receive support via traditional means as an additional usual support control group (3). This group will be used to provide a comparator against which the support provided to the regional and remote families can be judged.

The protocol for this study is registered with the Australian Clinical Trials Registry (ACTRN 012606000487516) and has been approved by the Royal Children's Hospital and Health Service District Ethics Committee and the University of Queensland Behavioural and Social Sciences Ethical Review Committee.

### Participants

Patients of the Royal Children's Hospital Haematology, Oncology and Stem Cell Transplant Unit will be identified by their paediatric oncologist before first discharge home. To be included in the study patients will be: newly diagnosed male or female paediatric oncology patients aged 2–18 years. Patients will be excluded if a home telephone connection of satisfactory quality cannot be installed.

The paediatric oncology clinical nurse consultants responsible for each patient will approach the family individually. Families will be asked to participate in a project investigating the use of videotelephones for supporting children with cancer and their families. A brief overview of the project will be provided before each family is asked if they consent to talk with a research assistant about the project.

The research assistant responsible for the project will provide written information on the trial informing all potential participants about the study, the frequency, content and expected duration of telephone interviews and what their participation would entail before obtaining consent.

### Randomization

An independent researcher with no direct involvement in the trial will be responsible for random allocation. A table of random numbers will be generated. Even numbers will denote allocation of regional and remote participants to the control group and odd numbers to the intervention group. Allocations to either group based on the table of random numbers will be written on a piece of paper and sealed in sequentially numbered opaque envelopes. As regional and remote families are enrolled in the trial, the research assistant will obtain information on allocation from the envelopes in sequential order and assign participants to their designated group. Due to the interactive nature of the intervention it is not possible to blind clinicians providing the intervention or participants involved in the study.

### Interventions

#### Usual care

All patients regardless of location are conventionally supported at first discharge home by the specialist multidisciplinary team of medical, nursing and allied health professionals. This is either done face-to-face during outpatient clinic visits or during subsequent inpatient stays, or via telephone to families who live far from the hospital. Telephone calls between specialist team members and families at home are used to assist with: problems that arise, clinical assessment and management and to provide education and counselling. Patients and families in the usual support control groups (i.e., all metropolitan families and those regional and remote families randomly allocated to the regional and remote control group) will have access to all of these standard services and facilities.

#### Videotelephone support

Patients randomly allocated to the regional and remote intervention group will have access to all of the usual support plus the videotelephone service. The videotelephone service can be used for: education, communication, counselling and monitoring with specialist multidisciplinary team members. The videotelephone service will be available to families for a 12-week period following first discharge home (families will be able to request a videotelephone call with team members at any time, the oncology clinical nurse consultant will call the family home twice a week for the first four weeks and weekly thereafter using the standard telephone and will initiate subsequent videotelephone calls with team members as required). In addition, the videotelephone will be available to family members to facilitate intra-family support during inpatient stays.

### Measurement

The SF-12v2 will be used to measure the primary outcome measure, parental health related quality of life. The SF-12 is a valid and reliable measure [30,31] used in a number of countries including Australia. More recently the SF-12 has been used in caregiver quality of life research [32].

Secondary outcome measures for parents will be: the informational/emotional subscale of the Medical Outcomes Study (MOS) Social Support Survey (a valid and reliable instrument for quantifying social support [33]), the 4-item Perceived Stress Scale (PSS) [34] and the FAMCARE scale (a valid and reliable instrument designed specifically to assess satisfaction with advanced cancer care [35]). For patients and siblings the Pediatric Quality of Life Inventory (Peds QL) parent proxy will be used (a valid and reliable measure of quality of life in children applicable to healthy populations and those with chronic disease [36]). In addition the Health Utilities Index Mark 2 (HUI2) will be completed by parents and used to assess patient quality-adjusted life years (QALYs).

Data collection will be undertaken via: user logs, chart audits, service database reviews, telephone and in-person interviews. Data collection with parents will begin at baseline (after consent has been obtained). The interviewer will be blinded to group allocation. Interviews will be used to obtain: demographics, baseline SF-12 scores, baseline informational and emotional support scores, baseline patient and sibling quality of life scores, and baseline satisfaction scores.

To reduce participant burden the completion of the various interview components will be staggered (Table 1). The initial interview will be the longest.

**Table 1 T1:** Interview schedule.

Component	Week												
	0	1	2	3	4	5	6	7	8	9	10	11	12
Demographics													
SF-12v2													
Informational/emotional support													
Perceived stress													
Patient quality of life													
Sibling quality of life													
HUI2													
Satisfaction													
Health care utilisation													
Family costs													

### Data analysis

#### Sample size calculations

A total of 162 participants will be included in the study (based on data provided by the tertiary paediatric oncology referral centre this is feasible for a 24-month trial with a 20% refusal/attrition rate), 108 in the control group – 54 metropolitan and 54 regional and remote, and 54 in the regional and remote intervention group. Sample size calculations are given for the two main comparisons and economic analyses:

1. Regional and remote intervention group vs regional and remote usual support control group

- To test whether the provision of videotelephones to families in regional and remote areas can improve the health related quality of life of parents caring for a child with cancer over usual care, a unpaired t-test of the mean difference will be used [38]. This will be based on the SF-12 at week 12.

- As no paediatric caregiver research using the SF-12v2 has been undertaken in Australia to date, published evidenced available on paediatric parental caregiver burden in the US [39] and US norms [31] (Table 2) have been used as a guide for the sample size calculation. A clinically important difference would be to improve mean mental health related quality of life of parents (SF-12 Mental Component Summary [MCS]) in the intervention group by 7.5 points. This figure is further supported by calculation of SF-12v2 standard error of measurement [SEM], calculated as the standard deviation of an instrument multiplied by the square root of one minus its reliability coefficient [40]. With an SD of 10 and reliability coefficient of 0.86 [31], the MCS-12 has an SEM of 3.74. Evidence by Wywrich [41] supports the use of one SEM as an approximation of the *minimal *clinically important difference [MCID] of a psychometric instrument. Using this approximation, an improvement in MCS-12 of 7.5 represents two times the MCID, which is a large clinically important difference.

**Table 2 T2:** Published evidence available on the SF-12 health-related quality of life instrument.

Context	n	Details	Mean	SD
The impact of paediatric tracheotomy on parental caregiver burden and health status (US)[39]	154	PCS-12 MCS-12	50.5 35.8	11.3 11.4
US Norms[31]	7069	General US population		
		PCS-12	49.63	9.91
		MCS-12	49.37	9.75
		Depression		
		PCS-12	45.55	11.71
		MCS-12	37.40	10.76

- Based on an improvement in MCS-12 mean in the intervention group of 7.5, and using SF-12v2 norm-based scoring methods (US general population SF-12v2 mean of 50 and SD of 10 [31]), at a power of 90% and a two-sided significance level of 1%, a sample size of 108 will be required, i.e. 54 in the intervention group and 54 in the control group.

2. Regional and remote intervention group vs metropolitan usual support control group

- To test whether the provision of videotelephones to families in regional and remote areas can improve the mental health related quality of life of parents to a level equivalent to that of metropolitan families receiving usual support, a test of equivalence will be used (according to the equivalence method described by Matthews [42]).

- With a two-sided significance level of 1%, sample size of 54, a mean difference between groups of zero and an equivalence bound of plus/minus 7.5, the study has a power of 87.2% for finding a genuine equivalence.

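### The 24-month feasibility statement does not fit the article's own referral figures for the randomised stratum: they give about 86 to 96 regional and remote families after 20% loss, against the 108 required

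*Protocol article*

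**What the plan says.** Under Sample size calculations, the article sets 162 participants in three groups of 54: regional and remote intervention, regional and remote control, and metropolitan control. It cites the referral centre's data and says that "this is feasible for a 24-month trial with a 20% refusal/attrition rate". For the randomised comparison at week 12, "a sample size of 108 will be required, i.e. 54 in the intervention group and 54 in the control group", at 90% power and a two-sided 1% level. For the comparison of the intervention group with the metropolitan group, the stated equivalence power is 87.2% with 54 per group and bounds of plus or minus 7.5. The Abstract puts the total as a recruitment number: "We will recruit 162 paediatric oncology patients and their families".

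The referral figures are in the Background. "Each year the service cares for around 100 newly diagnosed patients", and "Around 60% of the families cared for by the RCH (Figure 1) live in regional and remote areas". The Figure 1 caption gives a count over a two-year window: "data provided by the Royal Children's Hospital January 2004 to January 2006, n = 180". Under Design, only regional and remote families are randomised; metropolitan families form a non-randomised comparison group.

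**The concern.** Two of the three groups, 108 of 162 families or 67%, must come from a stratum that is around 60% of the caseload. A total that looks feasible overall can therefore still fall short among the families who are randomised. On the Figure 1 count, 108 equals every regional and remote family expected in two years, which leaves no room for the 20% loss that the plan itself assumes.

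The meaning of 54 per arm is also unsettled. The calculation produces it as a number analysed at week 12, while the Abstract and the sample size paragraph use it as a number recruited or included. The 20% combines refusal before enrolment with attrition after it, so the text does not show where the loss falls. At stake are the stated power of the only randomised comparison and the stated trial duration.

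**Working it through.** **Inputs from the article.** New patients in 24 months: 2 × 100 = 200 (Background), or 180 (Figure 1 caption, taken as 24 months). Regional and remote share: around 60%. Combined refusal/attrition: 20%. Difference 7.5 points, SD 10, two-sided alpha 1%, power 90%.

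**1. Reproduce the stated size.**

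n per arm = 2 × SD² × (z₀.₉₉₅ + z₀.₉₀)² / 7.5² = 2 × 100 × (2.576 + 1.282)² / 56.25 = 52.9, so 53 per arm and 106 in total.

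The stated 54 per arm has power 90.7% (normal approximation) or 89.6% (noncentral t). The 108 is therefore the number needed in the analysis. An allowance for 20% loss would make it 108 / 0.8 = 135.

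**2. Yield by stratum over 24 months.**

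| New patients | Regional and remote, before loss | After 20% loss | Metropolitan after 20% loss | Total after loss |
|---|---|---|---|---|
| 180 | 180 × 0.6 = 108 | 86.4 | 180 × 0.4 × 0.8 = 57.6 | 144 |
| 200 | 200 × 0.6 = 120 | 96 | 200 × 0.4 × 0.8 = 64 | 160 |
| Needed | | 108 | 54 | 162 |

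The regional and remote shortfall is 108 − 96 = 12 to 108 − 86 = 22 families (11% to 20%). The metropolitan group reaches its 54.

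**3. Does it matter where the 20% falls?** If it is all refusal, 86 to 96 are randomised. If it is all attrition, 108 can be enrolled (90% to 100% of the pool of 120 to 108), but 108 × 0.8 = 86 then have week-12 data. Enrolling the whole pool of 120 would leave 96. The analysed number is 86 to 96 in each case.

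**4. Sensitivity to rounding (an assumed range, since the article says only around 60%).**

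- 55% share: 180 × 0.55 × 0.8 = 79; 200 × 0.55 × 0.8 = 88.
- 65% share: 180 × 0.65 × 0.8 = 94; 200 × 0.65 × 0.8 = 104.
- Share needed for 135 families: 135 / 200 = 67.5%, or 135 / 180 = 75%.
- Both inputs high, 105 a year and 65%: 210 × 0.65 × 0.8 = 109, which just meets the target.

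**5. Power of the randomised comparison at the yield** (two-sided 1%, 7.5 points, SD 10):

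| Per arm | Noncentral t | Normal approximation |
|---|---|---|
| 54 | 89.6% | 90.7% |
| 48 | 84.9% | 86.4% |
| 43 | 79.8% | 81.6% |

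**6. Equivalence power.** Two one-sided t-tests at 1%, true difference zero, bounds ±7.5, SD 10. With 54 per group this gives 87.2%, the article's figure.

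| Intervention vs metropolitan | Power |
|---|---|
| 48 vs 54 | 83.9% |
| 43 vs 54 | 80.3% |
| 43 vs 43 | 72.6% |

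The last row applies only if 54 per group are enrolled and every group then loses 20%.

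**7. Time needed for 108 after 20% loss.** 135 regional and remote families at 60% means 135 / 0.6 = 225 new patients: 225 / 100 × 12 = 27 months at 100 a year, or 225 / 90 × 12 = 30 months at 90 a year.

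**The case against.** The strongest reply is that the inputs are too soft for a firm conclusion. Both Background figures are rounded, the proportions in Figure 1 are not shown, and the centre's data behind the feasibility statement are not given apart from the count of 180. That count also does not match around 100 a year, and the article does not explain the difference. At 65% and 100 a year the yield is 104, or 52 per arm with 88.2% power; slightly higher referral closes the gap. This stands as a limit on precision. It does not reconcile the text, because the target is met only when the inputs are pushed to or beyond the top of what the article's wording supports.

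A second reply is that the loss is moderate: about 80% to 85% power at a strict 1% level, with no test or error rate made invalid. That is correct, and it bounds the importance of the point.

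A reader might go further in four ways that the documents do not support:

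- *The trial cannot be delivered.* The shortfall applies to 24 months. The article calls that period feasible but does not say that recruitment closes then whatever the numbers.
- *The age limit and telephone-line exclusion reduce the pool further.* The article does not say whether its counts already leave such patients out, and gives no figure for either.
- *A full metropolitan group would conceal the shortfall.* Each group has its own target of 54, so a deficit in one would be visible.
- *Feasibility was checked only in total.* 200 × 0.8 = 160 is close to 162, but this is a guess about how the statement was made.

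**Conclusion.** The feasibility statement and the referral figures do not agree for the randomised stratum. On the article's point figures, 24 months gives about 86 to 96 regional and remote families with week-12 data, against 108 required. Power for the randomised comparison is then about 80% to 85% instead of 90%. The lower end rests on the count of 180 and the upper end on around 100 a year; since these two disagree, the 20% shortfall should not be treated as more certain than the 11% one.

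Equivalence power is about 80% to 84% if the metropolitan group fills to 54. A reader might take about 73% as the general consequence, but that figure belongs only to the reading in which all three groups enrol 54 and each then loses 20%.

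The result assumes a share near 60%, the stated 20% loss applied equally to both strata, SD 10, and a Figure 1 window of 24 months. A shortfall is likely but not certain, given the rounding.

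**What to change.** Amend the sample size paragraph in three respects.

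1. Give the feasibility arithmetic separately for regional and remote and for metropolitan families, using the centre's actual counts and share.
2. State whether 54 per arm is the number enrolled or the number analysed at week 12, and quote power at the analysed number for both comparisons.
3. Then choose one of two statements. Either give the 24-month regional and remote size as about 86 to 96, with power of about 80% to 85% at two-sided 1%; or keep 108 analysed and give the expected recruitment period for that stratum as about 27 to 30 months.

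If the centre's unrounded data do support 108 after loss within 24 months, showing them would settle the point instead.

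This is rewording and needs no new procedure. The cost is that either the stated power or the stated duration becomes less favourable, and the longer period would also carry the running costs of 3 to 6 more months of recruitment.

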- Families may also benefit financially from the improved support provided by the videotelephone service. Improved support has the potential to reduce the need for travel and associated costs. Information on family out-of-pocket expenses (such as travel costs including fuel, parking, fares; and other costs including meals, child care and accommodation) will also be obtained to assess the direct non-medical financial impact on families and how effectively the videotelephone service reduces this impact.

4. Cost-effectiveness analysis

- The health system perspective will be used for the primary analysis, and will be augmented in subsequent analysis with direct non-medical costs. The costs of providing the videotelephone service plus the total cost of health service use for the intervention group will be compared to the total cost of health service use identified in the regional and remote usual support control group. This is the incremental cost.

- Using the *Research Instruments *listed above, differences between the intervention group and the regional and remote usual support control group will be calculated. From this, the incremental cost per additional unit of benefit gained will be calculated, i.e. the incremental cost-effectiveness ratio (ICER); e.g. it costs an additional $x to improve parental quality of life by 1 point.

- A cost-utility analysis will also be undertaken. This allows comparisons between programs to be made and hence value for money judgements, as outcomes are standardised into quality-adjusted life years (QALYs). QALYs will be calculated using the HUI2 and the SF-6D algorithm to convert the SF-12 scores into utility scores (where 0 = dead, and 1.0 = best imaginable health state) and multiplied by the duration of life in that health state [37]. Differences in QALYs (for both parents and patients) between groups will be used to estimate the incremental cost-utility ratios.

- Sensitivity analyses will be conducted around the variables with the greatest uncertainty as well as the duration of final utility score at the end of the 12-week follow-up.

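### The announced economic sample size calculation is absent, and the cost-effectiveness ratios are planned with no stated measure of sampling error and no stated baseline adjustment

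*Protocol article*

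**What the plan says.** The Background part of the Abstract states: "The primary aim of this work is to investigate the cost-effectiveness of videotelephony". The third hypothesis is: "Using videotelephony will be a cost-effective method of service delivery". The Methods/design part of the Abstract names a different kind of quantity as the main endpoint: "The primary outcome measure is parental health related quality of life". It lists cost among the secondary outcomes.

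Under Sample size calculations the article announces: "Sample size calculations are given for the two main comparisons and economic analyses". Two numbered items follow. The first is superiority over the regional and remote control: "Based on an improvement in MCS-12 mean in the intervention group of 7.5", with "US general population SF-12v2 mean of 50 and SD of 10", 90% power and two-sided 1%, giving 54 per arm. The second is equivalence with the metropolitan control, with bounds of plus or minus 7.5 points and 87.2% power. There is no third item.

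Under Economic analysis, item 4, "the incremental cost per additional unit of benefit gained will be calculated, i.e. the incremental cost-effectiveness ratio (ICER"). Cost-utility ratios are then formed from differences in QALYs between groups, for parents (SF-6D from the SF-12) and for patients (HUI2). On uncertainty the section says: "Sensitivity analyses will be conducted around the variables with the greatest uncertainty". It adds the duration of the final utility score after the 12-week follow-up.

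**The concern.** The article says that an economic calculation is present, and it is not. A condensed article may leave detail to a fuller document, but this one states that the calculation is given. A reader would wrongly take the 162 families as sized for the cost-effectiveness question as well.

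The result planned for that question is a ratio. Varying its inputs shows dependence on assumptions. It does not show how far the ratio would move if another 54 families per arm were recruited. A ratio is also hard to interpret when its denominator may be near zero or change sign: the same negative value can mean cheaper and better, or dearer and worse. Finally, if QALY differences are taken as worded, without adjustment, whatever part of a chance baseline difference in utility persists to follow-up is counted as effect.

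**Working it through.** **1. The two stated figures are MCS-12 calculations.** Inputs from Sample size calculations: difference 7.5, SD 10, two-sided 1%, 90% power, 54 per group.
- Superiority: n per arm = 2 × [10 × (2.576 + 1.282) / 7.5]² = 52.9, so 53, against 54 stated. Power at 54 is 90.7% (normal) or 89.6% (t). This reproduces.
- Equivalence: two one-sided t tests at 1% each, margin 7.5, true difference 0, 54 per group, give 87.2%. This matches exactly.

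Neither figure uses a cost, a utility or a willingness-to-pay value.

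**2. The economic calculation cannot be reconstructed.** It would need the SDs of cost and QALY, their correlation, a willingness-to-pay value and a target net benefit. None is stated.

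**3. What 54 per arm offers on net benefit (illustration; the standardised differences and the 5% level are assumed).** The standard error in SD units is √(2/54) = 0.192.
- 95% interval half-width: 1.96 × 0.192 = 0.38 SD.
- Detectable difference: (1.96 + 0.84) × 0.192 = 0.54 SD at 80% power, and 0.62 SD at 90%.

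| Assumed difference (SD) | Power at 54 per arm, two-sided 5% | n per arm for 80% power |
|---|---|---|
| 0.2 | 18% | 393 |
| 0.3 | 34% | 175 |
| 0.5 | 74% | 63 |

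At the 1% level used for MCS-12, power is 6%, 15% and 51%.

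**4. Is a near-zero denominator plausible?** It depends on which ratio is meant.
- Cost per MCS-12 point: SE = 10 × 0.192 = 1.92. The planned 7.5 points lie 7.5 / 1.92 = 3.9 SE from zero, so instability is not a concern if the planning effect is real.
- Cost per QALY: 12 weeks is 12/52 = 0.231 years. An assumed sustained utility gain of 0.05 (range 0.02 to 0.10) gives 0.0115 QALY within follow-up (0.0046 to 0.0231), or half that if the gain builds up linearly. The small absolute size proves nothing, because the 0.231 scales effect and SE alike. What matters is gain over SE. With an assumed utility SD of 0.10 to 0.15, SE = SD × 0.192 = 0.019 to 0.029. A gain of 0.05 is then 1.7 to 2.6 SE from zero, a gain of 0.02 only 0.7 to 1.0 SE, and a gain of 0.10 3.5 to 5.2 SE. At 0.02 the observed difference would have the wrong sign about 15% to 24% of the time. At 0.05 it would do so about 0.5% to 4% of the time.

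**5. Baseline imbalance.** With the same assumed SDs, a one-SE chance difference in baseline utility is 0.019 to 0.029. If a fraction b of it persists (b between 0 and 1), it adds b × 0.019 to b × 0.029 to the follow-up difference. That is b × 38% to b × 58% of an assumed gain of 0.05. The full amount applies only if b = 1.

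**The case against.** The missing calculation can be called a slip of wording, cured by deleting a phrase. The rest can be called silence: intervals, bootstrap methods, willingness-to-pay ranges and baseline adjustment are commonly left to a fuller protocol or analysis plan. The text does not say that QALY differences will be unadjusted; it does not mention adjustment at all. The sensitivity analyses cover several variables and are not described as one-way. The cost per point is only an example within four planned areas of economic work. An effectiveness endpoint under a cost-effectiveness aim is also coherent, since SF-12 supplies the effect side of the ratio.

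Much of this stands, and it limits the point. It does not explain an announced calculation that is absent. Nor does it change the fact that the only uncertainty method the article names does not address sampling error.

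A reader might infer that the trial cannot say whether hypothesis 3 holds. The documents do not support that. Costs and utilities are collected in both randomised arms, so intervals and net benefit can be computed, and a missing power statement leaves precision unknown without ruling out a conclusion. A reader might also infer that the primary aim should be changed to the MCS-12 comparison. That is the sponsor's trade-off, and no correction of an error is involved.

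**Conclusion.** The point holds in limited form. The article claims an economic sample size calculation that it does not contain, and 54 per arm is justified only for MCS-12. As written, hypothesis 3 would rest on ratios whose sampling error is unstated, and chance baseline differences in utility could remain in the QALY comparison.

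The size cannot be fixed from the document. On assumed standardised net-benefit differences of 0.2 to 0.5 SD, power at two-sided 5% runs from 18% to 74%. Instability of the ratio is a concern for QALYs if the true utility gain is small, and not for MCS-12 at its planned effect. Both the instability and the imbalance figures rest on an assumed utility SD of 0.10 to 0.15 and an assumed gain of 0.02 to 0.10. Only the part of an imbalance that persists to follow-up matters.

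**What to change.** - In Sample size calculations, delete the reference to economic analyses. State that the economic evaluation is estimation without a powered test.
- In Economic analysis, item 4, estimate the parent QALY difference between the two randomised regional arms by regression adjusted for baseline SF-6D utility, which comes from the baseline SF-12 already planned. Adjust patient QALYs for baseline HUI2 if it is collected; the text does not list it by name among the baseline measures, and the marks in the interview schedule are not legible here.
- Report incremental net monetary benefit with bootstrap intervals and an acceptability curve over a range of willingness-to-pay values. Keep the ICER as a summary and the planned sensitivity analyses as they are.

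This needs no new families and, for parents, no new data. The cost is some extra analysis work and an economic conclusion that is openly unpowered.
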